## Abstract

**Background:**

The holistic health and wellness Kneipp concept, has a long tradition in Europe with demonstrated health benefits. Based on the five elements of the Kneipp concept, kindergartens in and around Germany are used to certify “Kneipp Kindergartens” that practice regular Kneipp applications and activities: cold water applications, exercise, nutrition, herbs and mind-body interventions. Little is known about the potential health benefits for children, however. This study protocol describes our study design and intervention of the Kita Kneipp Study to investigate the effect of the Kneipp concept on kindergarten children aged 2–6 years.

**Methods and design:**

The Kita Kneipp Study, registered with the German Clinical Trial Register (DRKS-ID: DRKS00029275), is a confirmatory, mixed-method, two-armed, waitlist, clinical, cluster randomized controlled trial (RCT). Kindergartens in Berlin, Germany that would like to implement the Kneipp concept into their facility will be recruited and randomized to the intervention or control group. Changes in the number of kindergarten sick days will be the primary outcome measure. Kindergarten attendance and reason for absence including illness will be collected on a weekly basis at two time points for 6 weeks from the parents and kindergarten directors: baseline and 1 year after baseline. Secondary outcomes will measure cold symptoms through the Common Cold Questionnaire (CCQ) and National Cancer Institute – Common Terminology Criteria for Adverse Events (NCI-CTCAE) Scales describing gastroenterological-based symptoms Kindergarten educator sick days will be aggregately reported for the same time period. Kneipp concept activities will be recorded on a weekly basis over the one-year intervention period. To understand the experience of Kneipp concept implementation and possible changes in the kindergarten, expert interviews will be conducted with intervention kindergarten educators and focused ethnographies will be planned to observe and analyze the intervention activities.

**Discussion:**

This mixed method study design has potential to help identify if the Kneipp concept can be used for salutogenic purposes among young children and provide insights and experience of the implementation and practicing a holistic health and wellness concept in a kindergarten setting.

## Introduction

1

Kneipp therapy is a holistic health, lifestyle and wellness approach that is embedded within German traditional medicine, based on complementary and naturopathy health concepts. The concept is named after the German priest and healer Sebastian Kneipp (1821–1897) who promoted the use of cold-water application from hydrotherapy in combination with a holistic health concept. Five principal elements are used for maintaining and sustaining health: temperature stimuli through cold (and warm) water applications, exercise, wholesome, plant-based, regional and seasonal nutrition, herbs and mind- body approaches (see Figure 1: Five Elements of Kneipp). This system, known as Kneipp therapy, is most well-known in German speaking countries and has one of the largest lay organizations for health and wellness in Germany (1). Kneipp therapy is used by trained and untrained practitioners in health promotion and for the prevention against diseases across a lifespan (2).

**Figure 1 fig1:**
[figure not shown]
Five Elements of Kneipp.

Childhood infection, especially in young children, creates a societal burden because a sick child at home requires a caregiver, who often must take a free day off work (3). Children and educators often experience cross-infections in kindergartens, contributing to the total burden of illness (4).

There is extensive research about the positive effects of a healthy diet and exercise on children’s overall health (5, 6). However, there is further research needed on Kneipp interventions especially with focus on the (cold) water applications and their effects on children’s health.

In a recent systematic review, evidence of the effects of Kneipp therapy across the life cycle were summarized; beneficial effects were noted for a wide range of conditions including varicose veins, menopausal syndrome, fever in children, absenteeism related to upper respiratory tract infections, hypertension, mild heart failure, sleep disturbances, cognition, and emotional functioning (7). The overall health benefits for children are inconclusive however, and few studies have been conducted with children and Kneipp therapy. Two pilot studies conducted with children aged 3–6 years that provide the foundation for this study found no significant reduction in infections through secretory IgA or fever but did demonstrate a lowered number of sick days for this sample (8, 9).

German kindergarten facilities, daycares through preschool system caring for young children between the ages of one to 6 years old, are currently being certified with a Kneipp concept that implements all five elements in the day care setting (10). Therefore, investigating whether a possible correlation exists between an implemented Kneipp concept and the number of absent sick days of children in such facilities would be of interest. For this purpose, we have planned a study with the aim to evaluate effects by monitoring absent sick days of children in kindergartens intending to implement a Kneipp concept and comparing this to data from kindergartens who are waitlisted to implement the Kneipp concept until after the study data has been collected. In order to evaluate the process of the concept-implementation and experiential dynamics, a qualitative approach will be used.

The following study questions will be examined:

– Quantitative hypothesis: Will the implementation of a child-friendly Kneipp concept in kindergartens improve health of kindergarten children aged 2–6 years, resulting in fewer illness-related absences from the kindergarten?– Qualitative research question: How does the kindergarten-appropriate implementation of the holistic health and wellness Kneipp concept change the overall quality of work, dynamics, and atmosphere within the kindergarten?

## Methods

2

The Kita Kneipp Study is a confirmatory, mixed-method, two-armed, waitlist, clinical, cluster RCT that was registered with the German Clinical Trial Register (DRKS-ID: DRKS00029275) on November 10, 2022 (submission for registration June 22, 2022), and approved by the Ethics Committee of the Charité - Universitätsmedizin Berlin (Application number: EA2/122/22, approved on September 13, 2022). It follows the standards of the Helsinki convention of good clinical practices.

This study protocol follows the SPIRIT (Standard Protocol Items: Recommendations for Interventional Trials) Guidelines for reporting study protocols (11).

### Study setting

2.1

Prior to study data collection, the study team interviewed already-certified kindergarten directors to find out aspects of the Kneipp concept that worked well in the kindergarten setting or were potentially problematic. This expert input was used to adapt our study design to the recruited facilities.

Kindergartens that had interest in becoming certified as Kneipp kindergartens and whose personnel wanted to take part in an applied Kneipp training for kindergartens were to be recruited to the study through contacts at the Berlin Senate level who have access to a network of Berlin kindergartens. A requirement for participation is the willingness of the facilities to be randomized. Further, inclusion criteria stipulated that the kindergarten facilities be compatible for Kneipp interventions, for example that they had suitable shower facilities, outdoor spaces, and room for indoor exercise (12). Included kindergartens will be recruited in Berlin, Germany. Informational evenings are to be held with kindergarten directors, caregivers and personnel to inform about the project, and to answer questions about the study purposes, design, data protection and inclusion. Written consent for participation in the study is required from all caregivers and educators.

The study will be conducted with two-time measurement periods, each 6 weeks long. Parents will complete an online at the end of each week of the data collection period. At the beginning of each measurement period, parents will be asked to complete an initial onboarding questionnaire containing socioeconomic background information about the family. The first measurement period will be planned in autumn 2022, followed by a second measurement in the autumn of 2023. Kindergarten directors will also be asked to record absences and reasons for absence of the participating children and educators and report them after completion of each 6-week data collection period.

The quantitative data of the study will evaluate the number of sick days and symptoms for children aged 2–6 years in kindergartens that implement kindergarten-appropriate, Kneipp applications, compared to the kindergartens in the waitlist group.

### Eligibility criteria

2.2

Eligibility crite shown in Table 1.

**Table 1 tab1:** Eligibility criteria.

	Inclusion criteria	Exclusion criteria
Kindergartens	Berlin kindergartens seeking certification as Kneipp daycare facilities with Kneipp-Bund e.V. Interested in participating in associated training via Sebastian Kneipp Academy. Willingness to engage in pair-randomized group assignment. Must provide pedagogical staff for training as Kneipp educators in autumn 2022 or 2023/24. Implementation of Kneipp concept immediately after training.	Kindergartens already implementing holistic health concepts (e.g., Kneipp, anthroposophical). Staff restricted from participating in training. Facilities unsuitable for implementing the Kneipp concept. Daycare center involved in another study preventing participation in this one.
Educators	Healthy educators, regardless of gender Working in the participating facilities 18–65 years of age Informed consent available	Serious chronic or acute illnesses inhibiting participation. Not speaking or understanding German
Caregivers	Caregivers, regardless of gender 18 years and older At least one child in a participating daycare center included in the study. Informed consent available	Serious chronic or acute illness preventing participation in the data collection. Not speaking or understanding German at the appropriate level for reading and completing study information
Children	Healthy children, regardless of gender 2–6 years Care in the participating kindergartens during study period Consent of the caregivers	Serious chronic or acute illness Not speaking or understanding German Age under 2y/o

### Interventions and blinding

2.3

Prior to being randomized into the group, kindergartens will be matched-paired according to socio-demographic information for Berlin neighborhoods and address (13, 14). Then kindergarten pairs will be cluster-randomized via computer randomization program by a team member without prior or background knowledge of kindergartens into the immediate start or waitlist group. Once they are allocated by the randomizing computer program into intervention or waitlist groups, they will be informed which group they are in. If a kindergarten declines to take part in the study based on group allocation, another replacement kindergarten will be selected for the recruitment vacancy.

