### Recruitment, randomization, and assignment of intervention

2.6

Gate keepers at the Berlin governing structures responsible for kindergartens, contact leads from cooperative partners in Berlin will identify interested kindergartens. Members of the study team (SB – experienced scientific researcher, study coordination, AT – study administration) will contact these via email in which a flyer about the project will be included as additional information. Once interested, kindergartens will be contacted via telephone and site feasibility will be assessed for inclusion.

After being recruited to the study, kindergartens with a similar socio-economic level will be match-paired according to statistical demographic analysis of locations in Berlin (14).

The kindergartens will then be randomized within their matched pair to either the intervention or the waitlist group using the randomizing function of Python 3.10.6, executed by an experienced biostatistician (FK). The allocated study group will not be blinded, as this would not be possible due to the nature of the interventions. Therefore, the kindergartens, caregivers and children will be aware whether they are in the Kneipp or in the waitlist group.

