**Figure 3 fig3:**
[figure not shown]
Data collection flowchart.

All teachers and caregivers will be informed about the purpose and implementation of the data collection as part of the evaluation via printed information sheets. The educator’s and parent’s written consent to participate will be collected (on paper) by the kindergarten directors. The following data will be recorded: Name, gender, date of birth, email, telephone number. Consents will be filed in a project folder and stored in a lockable office belonging to the kindergarten directors. The folders will be periodically checked during site visits by the study team (SB, MG – medical doctoral student, study coordination).

Focused ethnographies will be planned with the kindergarten staff to ensure that visits coincide with planned interventions. Based on these visits, willing staff will be asked to participate in a separately scheduled expert interview. Interviews will be audio-recorded, auto-transcribed via f4x (audiotranskription.de), corrected and pseudonymized. Transcripts and observation protocols will be uploaded and analyzed on a single computer with the qualitative analysis software MAXQDA 24 (Release 24.2.0).

At the beginning of the study, the study coordinator (SB) will create an electronic folder with a pseudonym for each participating kindergarten on a secure server. Documentation files with the following data will be stored in this folder:

– Main target parameters (missed days because of an infection)– Secondary target parameters (CCQ)– Interview audio and transcripts– Interview and observation field notes.

All results will be analyzed through anonymous aggregated data (quantitative part) or with the use of pseudonyms (qualitative part).

All collected study data will be collected and handled conforming to the Berlin Data protection Law (Berliner Datenschutzgesetz – BlnDSG) and in adherence with the Declaration of Helsinki code of ethics. The files will be stored in their anonymized and/or pseudonymized form after completion of the study on a Charité server for 10 years. Within the electronic survey system (SoSci), the participants are encrypted using IDs and are therefore not identifiable. The study coordinator (SB) will store the encryption list and will keep it in a locked cabinet. Access to the collected data will be restricted to members of the study team (SB, AT, MG, MB, GS, SW).

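### Kindergartens learn their arm at allocation and may be replaced if they decline because of it, while caregiver consent and the six-week baseline are not tied to precede disclosure

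*Protocol article*

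**What the plan says.** Section 2.6 of the protocol article starts the sequence at kindergarten level: "After being recruited to the study, kindergartens with a similar socio-economic level will be match-paired". Randomisation within the pair follows. Section 2.3 then says: "Once they are allocated by the randomizing computer program into intervention or waitlist groups, they will be informed which group they are in". The next sentence there leaves participation open after that: "If a kindergarten declines to take part in the study based on group allocation, another replacement kindergarten will be selected for the recruitment vacancy".

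Other sections bear on the timing:

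- **Consent.** Section 2.1 requires it from all caregivers and educators. Section 2.7 says that "written consent to participate will be collected (on paper) by the kindergarten directors", without saying when.
- **Awareness of the arm.** Section 2.6 states that "the kindergartens, caregivers and children will be aware whether they are in the Kneipp or in the waitlist group", again with no time attached.
- **Baseline.** Section 2.4 puts it before the intervention. Section 2.1 gives the season: "The first measurement period will be planned in autumn 2022". Table 1 gives the training slots as a kindergarten criterion: "Must provide pedagogical staff for training as Kneipp educators in autumn 2022 or 2023/24".
- **Analysis.** The primary model in Section 2.8 is a negative binomial regression on group and baseline sick days. The intention-to-treat set is the children for whom kindergarten reports exist.

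**The concern.** Randomising kindergartens protects the comparison only if the children counted in each arm are fixed without regard to the arm. If a kindergarten can leave once it knows its arm, or if families decide on consent once they know it, the two groups may differ in illness or attendance habits before any Kneipp activity starts.

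The baseline count is the plan's only adjustment for such a difference. A six-week count measures a child's underlying tendency to be ill with much noise, so adjusting for it removes only part of an enrolment difference. If the baseline is itself reported with the arm known, it can add a bias of its own. Over-reporting in the intervention arm would favour Kneipp; under-reporting would work against it.

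At stake is the confirmatory primary comparison of sick days.

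**Working it through.** **1. What the written order fixes.**

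| Step | Position in the readable text |
|---|---|
| Kindergarten recruited, matched, randomised | In that order (2.6, 2.3) |
| Kindergarten told its arm | After allocation, with no condition attached (2.3) |
| Kindergarten may decline because of its arm | After disclosure (2.3) |
| Replacement kindergarten enters | After the decline; no re-randomisation stated (2.3) |
| Caregiver consent | No position given (2.1, 2.7, 4.2) |
| Six-week baseline | Before the intervention (2.4), autumn 2022 (2.1) |
| Intervention-arm training | First slot in autumn 2022 (Table 1) |

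The clearest consequence is for replacements. A replacement fills a vacancy in a pair that has already been allocated. With no new draw, its arm is fixed before it joins. For children the text leaves the order open. For baseline, preceding the intervention is weaker than preceding disclosure. Neither the reporting-based intention-to-treat set nor the model anchors the analysis to children enrolled before allocation.

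**2. Size available for analysis.** Inputs from Section 2.5: φ = 0.205, two-sided α = 0.05, power 80%, dropout about 20%, stated total 240. For a chi-square test with 1 degree of freedom, N = (1.960 + 0.842)² / 0.205² = 187. Then 187 / 0.8 = 234, within 3% of 240. Evaluable children: 240 × 0.8 = 192, or 96 per arm. The order of steps does not change this number.

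**3. Illustration by simulation.** The documents give no shift, mean or dispersion, so these are assumed: no true effect, mean 3 sick days, a shared child-level frailty with variance 0.5, 192 children, no clustering or pairing. The model is negative binomial with group and baseline count.

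| Assumed lower underlying illness in the intervention arm | Adjusted rate ratio | Rejections at 5% |
|---|---|---|
| None | 1.01 | 3 to 6% |
| 5% | 0.97 | 5% |
| 10% | 0.96 | 8% |
| 20% | 0.85 to 0.91 | 14 to 17% |

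The range at 20% reflects how the counts are generated. With all extra variation in the shared frailty, the ratio is 0.90 to 0.91. Extra variation between the two periods makes baseline a weaker adjuster and moves the ratio towards 0.85.

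**4. Cross-check by normal approximation.** Let s be the shift in SD units and r the baseline-outcome correlation (assumed 0.3 to 0.5). The unadjusted standard error is √(2/96) = 0.144, and the adjusted one is 0.144 × √(1 − r²).

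- Enrolment shift in both baseline and outcome: remaining bias s(1 − r). With s = 0.2 and r = 0.5, the bias is 0.10 and the standard error 0.125. Their ratio is 0.80, giving a type I error of 0.126. With r = 0.3 it is 0.14 / 0.138, giving 0.174. With s = 0.1 the range is 0.069 to 0.080.
- Shift in reported baseline only: bias r × s in size. With s = 0.2, type I error is 0.072 to 0.126; with s = 0.1, 0.056 to 0.069.

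Both approaches agree that baseline adjustment reduces an enrolment bias but does not remove it, and that a small shift does little harm.

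**The case against.** The strongest reply is that much of this is silence in a condensed article. The full protocol is not at hand, and the data collection flowchart (Figure 3) is not shown; either may place consent and baseline first. That stands for caregiver consent and baseline. It does not answer the sentences on disclosure and replacement in Section 2.3, which state a procedure.

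A reader might infer that directors who already know the arm collect consent, and so that children are enrolled with the arm known. The documents do not say this. Section 2.7 names who collects consent but not when, and the right to decline in Section 2.3 concerns kindergartens, not families. Nor does a shared autumn show a conflict, since baseline could come first and training second.

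There are also safeguards. Kindergartens must be willing to be randomised (2.1, Table 1), and information evenings are described together with recruitment. All kindergartens sought Kneipp certification, and the waitlist receives the training later, so a contrast between families keen on Kneipp and others is muted. The Discussion concedes open-label reporting, caregiver response bias and possible allocation bias from pre-selection and cluster grouping, and it relies on double recording of the primary measure. These points make a large shift less likely. None covers entry after the arm is known.

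Finally, a 20% shift is large. If only one fifth of enrolled intervention children joined because of the arm and the rest matched the waitlist, that fifth would need no illness at all to produce it. If half did, they would need 40% less illness (0.5 × 40% = 20%). This is a fair limit on the illustration.

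**Conclusion.** The point holds in a limited form. The plan's own wording allows kindergartens to enter or leave with the arm known. It leaves open whether children do so, and whether baseline is reported with the arm known. That is a route for bias into the primary model; it is not evidence that bias occurred.

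Its size cannot be computed from the documents. Under the assumed shifts, false positives are about 5 to 8% for a 5 to 10% shift and 14 to 17% for a 20% shift, with an adjusted rate ratio of about 0.85 to 0.91 in the latter case. These figures ignore clustering and pairing and take the shift to favour the intervention. A reader might take them as the trial's expected error rate; nothing in the documents supports that.

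The change should be made, because it is standard, closes the route and costs little. Later disclosure alone would not be enough, since a kindergarten could still decline after it and be replaced.

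**What to change.** In Section 2.3:

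- State that caregiver consent, the list of enrolled children and the six-week baseline are complete in both kindergartens of a pair before allocation is generated, or at least before it is disclosed.
- Keep a kindergarten that declines after disclosure in the count of randomised clusters. Replace only by a new pair that is itself randomised.
- Report consent rates and declining kindergartens by arm.

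The article gives a registration date of 10 November 2022 and plans baseline for autumn 2022, so disclosure may already have taken place. In that case, report the dates of consent, baseline and disclosure for each kindergarten. Add a sensitivity analysis limited to originally randomised pairs and to children consented before disclosure, and name entry with the arm known among the limitations.

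Cost: if done prospectively, disclosure moves by about six weeks, which shortens the notice for releasing staff for training. Replacing by pairs means recruiting two kindergartens where one dropped out. The sensitivity analysis will contain fewer children, possibly many fewer if consent came late. The planned total of 240 does not change.

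### Section 2.3 lets a kindergarten leave because of its disclosed arm and be replaced, with no provision for randomising the replacement

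*Protocol article*

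**What the plan says.** The sequence is set out in the protocol article, sections 2.3 (Interventions and blinding) and 2.6 (Recruitment, randomization, and assignment of intervention).

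- Pairing comes first: "Prior to being randomized into the group, kindergartens will be matched-paired according to socio-demographic information for Berlin neighborhoods and address".
- Allocation is within the pair: "The kindergartens will then be randomized within their matched pair to either the intervention or the waitlist group using the randomizing function of Python 3.10.6".
- Disclosure follows: "Once they are allocated by the randomizing computer program into intervention or waitlist groups, they will be informed which group they are in".
- Then comes the replacement rule: "If a kindergarten declines to take part in the study based on group allocation, another replacement kindergarten will be selected for the recruitment vacancy".
- There is no masking of the arm: "The allocated study group will not be blinded, as this would not be possible due to the nature of the interventions".

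Two entry conditions bear on the rule. Section 2.1 (Study setting) says: "A requirement for participation is the willingness of the facilities to be randomized". Table 1 in section 2.2 (Eligibility criteria) lists, for kindergartens: "Willingness to engage in pair-randomized group assignment".

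Section 2.8 (Statistical methods) limits the intention-to-treat population to children with available kindergarten reports. The Discussion mentions possible allocation bias from socio-demographic pre-selection and cluster grouping, but not from replacement.

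**The concern.** A facility that refuses because of the arm it drew is lost by a process that can differ between arms. The facilities recruited are those seeking Kneipp certification and training, so a keen one may be unwilling to wait. The immediate arm brings a 40-hour training and, by section 2.10 (Harms), a possible extra time burden on educators, so a stretched facility may be unwilling to start. The substitute would be a facility content with the arm on offer.

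Motivation and staffing may be related to the primary outcome, because directors record the absences and the reasons for them. If so, the arms could differ for reasons other than the Kneipp concept. The substitute would also not be the facility that was matched to the remaining partner.

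What is at stake is the protection that randomisation gives to a confirmatory comparison of few clusters.

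**Working it through.** No figure in the plan supports the replacement rule, so there is none to reproduce. The 240 children in section 2.5 (Sample size) play no part in what follows. The check is a reading of the passages, then a bound on the weight of one replacement, then an illustration.

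**1. Is the vacancy's arm known?** Each pair sends one kindergarten to each arm. If one member leaves, its partner's arm determines the arm of the empty place. Section 2.3 discloses the arm before refusal is possible, and section 2.6 rules out masking. Those who fill the place, and the incoming facility, can therefore know the arm.

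**2. Is the replacement randomised?** Section 2.3 says only that it is selected. Neither 2.3 nor 2.6 describes redrawing the pair, a randomly ordered or pre-randomised reserve list, or re-matching. Section 2.3 assigns the draw to someone without background knowledge of the kindergartens, but that protects only the draw itself, not the later choice of a substitute.

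**3. Does the analysis recover it?** A kindergarten that declines and supplies no reports drops out of the intention-to-treat set as defined, and its substitute enters it. The primary negative binomial model adjusts for baseline sick days. That absorbs part of a stable difference in level, but not a difference in trend or in reporting.

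**4. Weight of one replacement.** Section 2.5 fixes no number of pairs. Two statements give an indirect ceiling on intervention facilities:

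- Section 2.3.1: every director and at least 2 other educators from each intervention facility are interviewed.
- Section 2.5: interviews with up to 15 educators.

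| Reading | Facilities at most | Share of one replacement |
|---|---|---|
| Directors count among the 15 | 15 / 3 = 5 | 1/5 = 20% |
| Directors are additional | 15 / 2 = 7.5, so 7 | 1/7 = 14.3% |

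These are ceilings on the number of facilities, so the shares are minimums. Pairing gives the waitlist arm the same number of kindergartens.

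**5. Illustration of bias, on assumptions only.** A simulation assumed no true effect, refusals only by keener-than-average waitlist kindergartens, less keen substitutes, and a correlation of −0.3 to −0.5 between keenness and cluster sick days. Cluster means were compared by a paired t-test without baseline adjustment.

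| Waitlist clusters replaced | Spurious difference favouring Kneipp (between-cluster SDs) |
|---|---|
| 0% | 0 |
| 10% | 0.05–0.08 |
| 20% | 0.09–0.16 |
| 30% | 0.14–0.24 |

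Two-sided type I error rose from 5% to at most about 6% with 6 pairs and about 8% with 10 pairs. Ten pairs exceeds the ceiling in step 4.

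**The case against.** The best defence is that the sentence is short and may be read too harshly. It gives no selection method and does not say outright that the substitute inherits the vacant arm. Section 2.6 describes the general order as recruit, pair, randomise, and filling a recruitment vacancy could mean going back to the start of that order. This is possible, but filling the empty place is the more natural reading, and if a fresh draw was intended the text needs to say so.

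Several stronger conclusions are tempting and are not supported:

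- **That substitutes are hand-picked.** The text says only that they are selected. The defect is that no mechanism is stated.
- **That the rule contradicts the entry criteria.** Willingness to be randomised is a condition of entry; the rule covers a facility that later goes back on it. The two can coexist, though they sit badly together.
- **That facilities will drop out asymmetrically.** No decline rate or reason is given. Table 1 also screens out facilities whose staff are restricted from the training and requires staff to be provided for it, which weakens the staffing mechanism. The most one can say is that they may.
- **That the comparison is no longer randomised.** Nothing is lost unless a kindergarten declines, and pairs without a refusal remain randomised and can be analysed on their own.
- **That the bias can be stated in sick days.** Any such figure would rest wholly on an assumed difference and an assumed mean.

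It is also fair to say that a refusing facility cannot simply be kept in the analysis. Child data need caregiver consent, which under section 2.7 is collected through the kindergarten directors. That limits the remedy but does not justify the rule.

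**Conclusion.** The point stands in conditional form. As written, section 2.3 permits arm-dependent replacement of clusters after randomisation and disclosure, and nothing elsewhere in the article closes the gap. A later analysis plan can limit the damage, by excluding affected pairs, but cannot turn a substitute into a randomised cluster.

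The size of any bias is unknown. One replacement would be at least about 14–20% of the intervention arm, if the interview numbers are a fair guide to how many facilities are planned. The simulated effect on type I error is modest and depends on its assumptions.

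The case for changing the rule rests on preserving randomised allocation in a confirmatory trial with few clusters, not on a demonstrated large bias.

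**What to change.** Replace the sentence in section 2.3 with a rule to this effect:

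1. Each director commits in writing to accept either arm before the pair is randomised.
2. No single vacancy is filled once the arm has been disclosed. Any vacancy is filled only by matching and randomising a complete new pair, or by a reserve pair randomised in advance.
3. A kindergarten that declines after allocation is shown in the flow diagram by arm and reason. Its absence records are used as allocated where consent permits; otherwise it is reported as a lost cluster.
4. If a replacement has already been made, which is possible because the first measurement was planned for autumn 2022, it is reported by arm, and a sensitivity analysis excludes the affected pairs.

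The cost is a change of wording and a commitment form. The downside is that a pair may occasionally be lost or a new pair needed.
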